**Attrition 30%~420**

**Attrition 30%~420**

**Branch 2**

**20%=600**

**Branch 3**

**20%=600**

**Branch 4**

**20%=600**

**Attrition 30%~420**

**Branch 1**

**20%=600**

**Control**

**60-day follow-up survey**

**Attrition 40%~360**

**60-day follow-up survey**

**60-day follow-up survey**

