**Sampling, Sample Size, and Statistical Power**

The three primary outcomes in this study are increased HIV testing, HIV disclosure, and condom use. Using historical data from the pilot intervention (see Appendix A), we observed that HIV testing increased from 20% to 42% in HIV-negative men between baseline and 3-month follow-up. Based upon these values using a 2-group design (control vs. intervention), with a 5% significance level and 80% power, 77 participants would be required in each study condition for a total sample size of 154. In the current study, which has a 5 branch design, we anticipate that by enrolling 3,000 men and retaining 70% (N=2,111), we will have sufficient power to detect meaningful differences in behavior among the study branches.

Although we will be comparing within and across all study branches, we expect the greatest differences to be found between control branch 1 and branch 5 (both videos) for the primary outcomes. The Bonferroni correction will be used to protect the overall Type I error rate with multiple comparisons. In these comparisons, the nominal significance level will be set to alpha = 0.05 for two-sided tests (divided by the number of pairwise comparisons for individual tests). Using Chi-square tests to detect behavioral changes between the binomial primary outcomes, we obtain the following powers to detect a difference between two study branches for various true proportions and sample sizes (α=0.05; 10 pairwise comparisons).

| **Power Calculations for Meaningful Differences**  **between Study Branches** | | | | | |
| --- | --- | --- | --- | --- | --- |
| **Behavior Change Outcomes†** | | **Sample Size per Branch* and Associated Power** | | | |
| Branch A | Branch B | N = 300 | N = 400 | N = 500 | N = 600 |
| 0.10 | 0.15 | 0.142 | 0.221 | 0.308 | 0.396 |
| 0.10 | 0.20 | 0.709 | 0.865 | 0.944 | 0.979 |
| 0.10 | 0.25 | 0.978 | 0.997 | >.999 | >.999 |
| 0.15 | 0.20 | 0.097 | 0.150 | 0.210 | 0.275 |
| 0.15 | 0.25 | 0.569 | 0.747 | 0.863 | 0.931 |
| 0.15 | 0.30 | 0.939 | 0.988 | 0.998 | >.999 |
| 0.20 | 0.30 | 0.476 | 0.652 | 0.784 | 0.874 |
| 0.20 | 0.35 | 0.894 | 0.971 | 0.993 | 0.999 |
| 0.20 | 0.40 | 0.994 | >.999 | >.999 | >.999 |
| 0.30 | 0.40 | 0.375 | 0.536 | 0.673 | 0.780 |
| 0.30 | 0.45 | 0.821 | 0.936 | 0.980 | 0.994 |
| 0.30 | 0.50 | 0.984 | 0.998 | >.999 | >.999 |
| 0.40 | 0.50 | 0.336 | 0.488 | 0.623 | 0.733 |

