**Attrition and Retention Efforts**

Sample selection procedures are designed to produce a sample of approximately 3,000 MSM (600 men per randomized branches 1-5) at the end of the recruitment period. Past formative work, which included piloting an internet-based intervention with a 90-day follow-up survey, showed an attrition rate of 45%, with slightly less than 500 of the 1,000 men who provided emails completing the follow-up survey. Given the shorter follow-up period (60 day follow-up) in this research study, we expect a lower overall attrition rate and a differential attrition rate by branch. We estimate that control branch 1 and standard text-based prevention web page branch 2 will yield an approximate attrition of 240 (40%) participants, and video treatment branches 3-5 will yield an approximate attrition of 180 (30%) participants. We are expecting higher attrition for branches 1 and 2 since there is no video component, which is more engaging.

We will make efforts to minimize study attrition by sending up to 4 reminder emails (Appendix C-3) to participants during the course of the follow-up period. For participants who do not respond to the follow-up email, we will wait approximately 1 week before sending a first reminder email, approximately another week before sending the second reminder, and approximately one more week before sending the final reminder email. In our previous work, virtually no additional responses were obtained after 3 reminders.

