***Title: Is HIV Still a Big Deal?***

***Baseline***

[name], PI

Between October 11 and 22, 2005 we conducted our first national online behavioral intervention on Manhunt.net (funding from the van Ameringen Foundation, The New York Community Trust, and The Shelley and Donald Rubin Foundation). **The Morning After** was designed to promote critical thinking about HIV disclosure, risky sexual behaviors and the complex beliefs and attitudes underlying these behaviors. Approximately 13,500 men clicked on the online banner ad, and out of those, 3,139 consented to participate in the intervention; 2,777 completed the baseline behavioral risk survey (pre-test); 1601/2777 watched the video about a sexual encounter between an HIV-positive and HIV-negative male; 1510/1601 completed the questions about HIV testing and disclosure after the video (post-test); and 1087/1510 consented to give us their email address for a follow-up behavioral risk survey in 3 months. Online, 1,002 men completed the baseline behavioral survey, watched the video, completed the post-video survey and provided valid email addresses for 3 month follow-up. The median age of men consenting to participate was 38.

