***Follow-up*: Validation of the Online Video as an Intervention**

Of the 1,002 men who completed the survey and provided emails, 3 months later, 908 emails were still working. Emails linking to the follow-up survey were sent 1/17, 1/23 and 2/1/06 to 908/1,002. No incentives were provided. Preliminary analysis compared disclosure of HIV status to sexual partners and HIV testing, before and in the 3 months after watching the video, by McNemar and Pearson Chi-square tests. Three months after watching the video, 496 of 908 men (55%) with working emails completed the follow-up survey. Men completing follow-up and those who did not were similar by race/ethnicity (14% Hispanic, 72% white, 6% black, 2% Asian, 6% mixed/other), age (mean 38) and prevalence of unprotected anal intercourse with a new/casual partner (36%), but were significantly more likely to have a college degree (55% vs. 47%, p=.01). Statistically significant behavior changes were found. Men were 3 times more likely to ask their partner’s HIV status (OR=3.0, p<.001) and two times more likely to disclose their own(OR=2.2, p<.001) at follow-up compared to baseline. The 318 HIV-negative men participating in the evaluation were also three times more likely to report HIV testing during follow-up (42%) than in the 3 months before baseline (20%) (OR=2.8, p<.001). These findings strongly suggest that online interventions designed to engage critical thinking are an efficient and effective way to influence behavior change in large numbers of at-risk MSM.

We examined the prevalence and stability of drug and alcohol use between baseline and follow-up. At baseline, 7% reported methamphetamine use in their last sexual encounter. At follow-up, 5% reported methamphetamine in their last encounter. Out of the methamphetamine users at baseline, 39% followed up and were significantly LESS likely than non-users to follow-up (OR 0.6, p<.05). Contrary to methamphetamine use, other drug use (i.e., poppers, marijuana, MDMA, GHB, cocaine) as well as alcohol use, reported between baseline and follow-up remained stable. Specifically, there were no significant differences in the proportions of men reporting drug or alcohol use at baseline compared to follow-up. Drug use at baseline and follow-up was 24% and 32%; alcohol use was 27% at both baseline and follow-up.

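### The power statement rests on 70% retention (N=2,111), but the protocol's own branch attrition leaves 1,980 men (66%); the pilot loss and the flow chart counts are also mis-stated, with a modest effect on power

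*Protocol*

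**What the plan says.** The protocol gives the retained sample in three places and describes the pilot loss in two.

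- *Sampling, Sample Size, and Statistical Power*: "by enrolling 3,000 men and retaining 70% (N=2,111), we will have sufficient power to detect meaningful differences in behavior among the study branches". The power table that follows uses 300 to 600 men per branch and ten pairwise comparisons, so alpha is 0.05/10 = 0.005 per test. A footnote warns that attrition may reduce the branch sizes.
- *Attrition and Retention Efforts*: recruitment aims at "approximately 3,000 MSM (600 men per randomized branches 1-5"). Branches 1 and 2 "will yield an approximate attrition of 240 (40%) participants, and video treatment branches 3-5 will yield an approximate attrition of 180 (30%) participants".
- Study design flow chart: three boxes read "Attrition 30%~420" and two carry 40% with 360.
- *Attrition and Retention Efforts*, on the pilot: it "showed an attrition rate of 45%, with slightly less than 500 of the 1,000 men who provided emails completing the follow-up survey".
- Appendix A, on the same pilot: 1,002 men gave valid addresses and 908 of these still worked at three months; "496 of 908 men (55%) with working emails completed the follow-up survey". Before that step, "1087/1510 consented to give us their email address for a follow-up behavioral risk survey in 3 months".

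**The concern.** The retained N is the only number that supports the claim of sufficient power. The section on minimum meaningful differences gives no numerical target; it defines a meaningful difference by statistical significance. A reader can therefore judge the claim only by taking the retained N to the power table. If that N disagrees with the attrition section, the reader enters the table at the wrong place.

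The pilot rate matters because it is the only empirical basis offered for the assumed loss. This trial randomises men once they consent and give an email address, and keeps them in their assigned group. An address that later fails therefore counts as attrition here, whereas the pilot's 45% leaves such addresses out.

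**Working it through.** **1. Retained N**

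Inputs (attrition section): 600 per branch; 240 lost in each of branches 1 and 2; 180 lost in each of branches 3 to 5.

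- Branches 1 and 2: 600 − 240 = 360 each.
- Branches 3 to 5: 600 − 180 = 420 each.
- Total: 2 × 360 + 3 × 420 = 1,980; 1,980/3,000 = 66.0%.
- Stated: 2,111, which is 2,111/3,000 = 70.4%. A flat 70% gives 2,100.
- Shortfall: 2,111 − 1,980 = 131 men, or 6.2% of 2,111.

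So 70% is the expected retention of the video branches alone.

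**2. Flow chart**

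30% of 600 is 180 and 40% of 600 is 240. The printed 420 and 360 are the men remaining. The percentages agree with the attrition section; the counts carry the wrong label.

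**3. Pilot loss**

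| Denominator | Men | Completed | Lost |
|---|---|---|---|
| Emails still working at 3 months | 908 | 496 | 45.4% |
| Valid email, all baseline steps done | 1,002 | 496 | 50.5% |
| Agreed to give an email | 1,087 | 496 | 54.4% |

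The 45% is right for 908. It cannot be right beside fewer than 500 completers out of 1,000, which is a loss of more than 50%.

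**4. Power**

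Method: two-proportion test with continuity correction, two-sided alpha 0.005 (z = 2.807):

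power = Φ{[|p1 − p2| − ½(1/n1 + 1/n2) − 2.807 × SE0] / SE1},

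where SE0 uses the pooled proportion and SE1 the separate proportions. This reproduces the protocol's table to within 1.3 percentage points (20% v 30% at N=400: 0.648 against the printed 0.652). Without the correction the gap is up to 3.3 points. The sample size of 77 per group for 20% v 42% also reproduces (77.0).

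Example, 20% v 30% at 360 v 420:

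- pooled proportion = (72 + 126)/780 = 0.2538
- SE0 = 0.03126; SE1 = 0.03073
- corrected difference = 0.10 − 0.00258 = 0.0974
- (0.0974 − 2.807 × 0.03126)/0.03073 = 0.315, so power = 0.62

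The stated N corresponds to 2,111/5 = 422 per branch. The column 360 v 420 covers branch 1 v 5 and five other pairs.

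| Comparison | 422 v 422 | 360 v 420 | 360 v 360 (branch 1 v 2) |
|---|---|---|---|
| 10% v 20% | 0.88 | 0.84 | 0.80 |
| 15% v 25% | 0.77 | 0.72 | 0.68 |
| 20% v 30% | 0.68 | 0.62 | 0.58 |
| 30% v 40% | 0.57 | 0.51 | 0.47 |
| 40% v 50% | 0.52 | 0.47 | 0.43 |
| 15% v 30% | 0.99 | 0.98 | 0.98 |
| 20% v 35% | 0.98 | 0.97 | 0.95 |
| 30% v 45% | 0.95 | 0.93 | 0.90 |
| 40% v 55% | 0.93 | 0.91 | 0.88 |

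**5. Detectable difference** (80% power, alpha 0.005, bases of 20-40%, same formula solved for the difference)

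- 422 per branch, as stated: 11.2 to 12.7 points.
- 360 v 420 (six pairs): 11.7 to 13.3.
- 360 v 360 (branch 1 v 2): 12.2 to 13.8.
- 420 v 420 (three pairs within branches 3 to 5): 11.2 to 12.8.

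**6. Sensitivity case: pilot-level retention**

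3,000 × 496/1,002 = 1,485 (297 per branch); 3,000 × 496/1,087 = 1,369 (274 per branch). Power for 20% v 30%, 30% v 40% and 40% v 50% is then 0.47, 0.37 and 0.33 at 297, and 0.42, 0.33 and 0.29 at 274.

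**The case against.** The strongest reply is that the error changes little, and most of that reply stands.

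- Ten-point differences from bases of 15-40% are already below 80% power at the stated 422 per branch. For branch 1 v 5 the detectable difference moves by only about half a point. No 10- or 15-point contrast examined crosses 80% at 360 v 420 because of the correction.
- The protocol does not hide the low power. Its N=400 column, which lies between the expected 360 and 420, prints 0.652, 0.536 and 0.488 for 10-point differences from 20%, 30% and 40%. The table goes down to 300. Showing columns for 500 and 600 is not an error, since 600 is the enrolment figure.
- The only effect size cited, 20% v 42%, has power above 0.99 at 360 v 420.
- The flow chart text may be read as the loss followed by the number left, and the attrition section states the losses correctly.

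A reader might infer two stronger conclusions. The first is that the trial is underpowered because of this error; the table in the working does not support that. The second is that the pilot loss of 50-54% forecasts the trial's loss. The protocol expects less loss because follow-up is 60 rather than 90 days. It gives no figure for that gain, but the pilot rate remains a sensitivity case. Its size also depends on the denominator: 297 per branch is practically the table's N=300 column, and only the less favourable 1,087 gives 274.

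None of this reconciles 2,111 with 1,980, or 45% with fewer than 500 of 1,000.

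**Conclusion.** The concern holds as a correction to stated figures. On the protocol's own branch attrition, 1,980 men (66%) are retained, which is 131 fewer than the number on which the power claim rests. The pilot loss is 50.5% on the denominator named in its own sentence, and 45% only on working emails. The flow chart labels retained men as attrition.

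The cost in power is about 4 to 6 percentage points for 10-point differences between branches 1 and 5, and about 8 to 10 points for most of them between branches 1 and 2. Fifteen-point differences from bases of 15-40% keep 0.91 or more at 360 v 420 and 0.88 or more for branch 1 v 2. This is not evidence that the trial is underpowered for every difference.

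The figures assume 600 men per branch, attrition as stated in the attrition section, alpha of 0.005 per pair, and a continuity-corrected comparison of proportions. If the sponsor holds 70% overall to be right, the branch attrition must change instead; the document does not settle which was meant.

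**What to change.** 1. Reconcile the sample-size section, the attrition section and the flow chart. If the branch attrition stands, state retention as 66% (N=1,980: 360, 360, 420, 420, 420).
2. Label 420 and 360 in the flow chart as retained, or print 180 and 240 as attrition.
3. Give the pilot loss with its denominator: 45.4% of 908 working emails, 50.5% of 1,002 valid emails, 54.4% of 1,087 who agreed to give one.
4. Replace the statement that power is sufficient with the detectable difference at 80% power and alpha 0.005, for bases of 20-40%: about 11.7-13.3 points for 360 v 420, 12.2-13.8 for branch 1 v 2, and 11.2-12.8 within branches 3 to 5. Recompute if the final alpha differs.
5. Show pilot-level retention (about 275 to 297 per branch) as a sensitivity case, labelled as such.

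The cost is wording and a recomputed table. The stated power becomes slightly less favourable. Design, enrolment, alpha and analysis do not change.

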†Behavior change outcomes refer to the primary outcomes of interest: HIV disclosure, testing, and condom use.

*We anticipate enrolling 600 per branch; however, attrition may yield smaller sample sizes.

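### Single-step Bonferroni on the ten branch pairs is valid, but Holm's step-down version gives the same familywise guarantee with modestly more power; an optional improvement

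*Protocol*

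**What the plan says.** The multiplicity rule is in the Protocol, section Sampling, Sample Size, and Statistical Power.

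- Method: "The Bonferroni correction will be used to protect the overall Type I error rate with multiple comparisons".
- Level: "the nominal significance level will be set to alpha = 0.05 for two-sided tests", and this is "divided by the number of pairwise comparisons for individual tests".
- Family used for the power table: "α=0.05; 10 pairwise comparisons", that is, all pairs of five branches.
- Test: "Using Chi-square tests to detect behavioral changes between the binomial primary outcomes".
- Example row (0.20 v 0.30 at 300, 400, 500 and 600 per branch): "0.20 | 0.30 | 0.476 | 0.652 | 0.784 | 0.874".

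No step-down, ordering or gatekeeping is described, so the same divisor applies to every pair whatever happens to the others.

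Two other places bear on the point. The section Specific Aims and Hypotheses puts branches 3, 4 and 5 against branches 1 and 2 for the primary outcomes, which is six of the ten pairs. The section Attrition and Retention Efforts expects that branches 1 and 2 "will yield an approximate attrition of 240 (40%) participants" each, and that branches 3 to 5 lose 180 (30%) each. The footnote to the power table also allows for this: "We anticipate enrolling 600 per branch; however, attrition may yield smaller sample sizes".

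**The concern.** Single-step Bonferroni keeps every pair at 0.005 even after other pairs have been rejected. Holm orders the p-values and compares the smallest with 0.05/10, the next with 0.05/9, and so on, stopping at the first failure. It needs no further assumption, has the same familywise bound, and can never reject fewer hypotheses.

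Its advantage appears when several null hypotheses are false, which is what the primary hypotheses predict. The protocol's own table shows that power for 10-point differences is limited at realistic completer numbers: at 400 per branch it is 0.652 for 0.20 v 0.30 and 0.536 for 0.30 v 0.40. At stake is some power on the later comparisons and on the chance of showing the whole hypothesised pattern.

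**Working it through.** **Inputs.** Two-sided familywise 0.05; ten pairs; chi-square test on two proportions (all from the sample-size section). Completers: 600 − 240 = 360 in branches 1 and 2, and 600 − 180 = 420 in branches 3 to 5 (attrition section). The protocol does not state the expected rates in each branch. The rates below are scenarios taken from its power table, graded values between 0.20 and 0.30, and the pilot's 20% and 42%.

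**Step 1: reproduce the printed table.** Power = Φ[(d − z·SE0)/SE1], with z = 2.807 for a two-sided 0.005. SE0 is the pooled and SE1 the unpooled standard error. For 0.20 v 0.30 at 600 per branch:

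- SE0 = √(2 × 0.25 × 0.75/600) = 0.0250
- SE1 = √((0.16 + 0.21)/600) = 0.0248
- Without continuity correction, d = 0.10: Φ(1.20) = 0.885
- With continuity correction, d = 0.10 − 1/600 = 0.0983: Φ(1.13) = 0.872, against 0.874 printed

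With the correction, all 52 cells of the table agree within 1.3 points. The table is therefore a single-step Bonferroni calculation at 0.005, as the text says.

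**Step 2: the two rules.** Bonferroni uses 0.005 for all ten tests. Holm uses 0.05/10, 0.05/9, …, 0.05/1 = 0.0050, 0.0056, 0.0063, 0.0071, 0.0083, 0.0100, 0.0125, 0.0167, 0.0250, 0.0500. The first step is the same.

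**Step 3: simulate both on the same data.** Completers 360/360/420/420/420; ten uncorrected chi-square tests per simulated trial; at least 60,000 trials per scenario. As a check, the closed form for 0.30 v 0.40 with 360 and 420 gives 0.542, and the simulated single-step value is 0.54 to 0.55.

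| Rates, branches 1 to 5 | Mean power over the six hypothesised pairs, Bonferroni → Holm | All six significant | At least one of the six |
| --- | --- | --- | --- |
| 0.30, 0.30, 0.40, 0.40, 0.40 | 54% → 59% | 13% → 21% | 92% → 92% |
| 0.20, 0.20, 0.30, 0.30, 0.30 | 66% → 71% | 23% → 33% | 96% → 96% |
| 0.20, 0.20, 0.25, 0.25, 0.30 | 30% → 32% | 0.7% → 1.5% | 84% → 84% |
| 0.20, 0.225, 0.25, 0.275, 0.30 | 27% → 28% | 0.3% → 0.8% | 77% → 77% |
| 0.20, 0.20, 0.42, 0.42, 0.42 | 100% → 100% | 100% → 100% | 100% → 100% |

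If only branch 5 works (0.30 against 0.20 elsewhere), branch 1 v branch 5 rises from 66% to 68%, and the chance of at least one of the six from 82% to 83%.

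**Step 4: familywise error, Bonferroni → Holm.** All branches equal: 3.9% for both. 0.30 v 0.40 pattern: 1.9% → 2.9%. 0.20 v 0.30 pattern: 1.9% → 3.0%. 0.20 v 0.42 pattern: 1.9% → 4.6%. Holm's realised error is higher once some pairs differ, but stays below 5%.

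**The case against.** Bonferroni is a legitimate choice, correctly specified, and the power table follows from it, so nothing is stated wrongly. That stands: this is a matter of efficiency.

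The 10-point scenarios with three equally effective video branches favour Holm. The protocol expects its largest difference between branches 1 and 5, which points towards graded effects, where the gain is small. At the one effect size the protocol takes from data (20% to 42% in the pilot), there is no gain. That also stands, although the pilot figure is a before-after change and not a difference between branches, so smaller effects are plausible.

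Bonferroni has two real advantages: simultaneous intervals that match its decisions, and a lower realised error when some pairs differ. Both are genuine, but the second lies inside the 0.05 bound that the protocol sets itself.

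A reader might infer two stronger things. The first is that single-step Bonferroni costs power with no difference at all in error. The figures in step 4 show otherwise: only the guaranteed bound is the same. The second is that Holm would lift the chance of winning all six pairs from 19% to 45% (0.30 v 0.40). That holds only for a family of six pairs, and the protocol fixes ten. Cutting the family to six with plain Bonferroni (0.05/6 = 0.0083) would by itself raise mean power per pair to 61%, slightly more than Holm over ten. The choice of family is a separate decision and should not be credited to the step-down rule.

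**Conclusion.** The protocol's multiplicity rule is valid and consistent with its power table. Holm on the same ten tests is a modest, cheap improvement. It adds about 4 to 5 points of power per hypothesised pair, and 8 to 10 points on the chance of showing all six, if the video branches share a 10-point effect. It adds about 1 to 3 points per pair if effects are graded or only branch 5 works, and nothing at effects as large as the pilot's. It hardly changes the chance of at least one significant hypothesised pair, because its first step is also 0.005.

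These sizes rest on assumed branch rates, the protocol's expected attrition, and binary outcomes tested by uncorrected chi-square. That Holm never rejects less and keeps familywise error at or below 0.05 does not depend on them. The point is optional.

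**What to change.** Replace the Bonferroni sentence with: *Pairwise p-values for each primary outcome will be adjusted by Holm's step-down procedure (two-sided familywise 0.05).* Align the clause that divides alpha by the number of pairs. Keep the power table and label it as the single-step lower bound. Make the change before any comparison of outcomes between branches.

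The cost is one sentence and one line of code. What is lost is a simple set of simultaneous confidence intervals that match the decisions. Report either Bonferroni-adjusted intervals or clearly labelled unadjusted ones beside the Holm-adjusted p-values, and say that they may not agree with every decision.

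This does not deal with multiplicity across the three primary outcomes, or with the different significance levels (.01 overall, .05 within branch) named in the section Data Handling and Analysis. Those are separate matters.
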